### Randomization and Allocation Concealment

The participants will be allocated randomly to one of the 2 sequences: ChatGPT (A), followed by conventional web-based tools (B), or conventional web-based tools (B), followed by ChatGPT (A). The allocation of participants into sequences (AB or BA) will be determined through computer-generated randomization in an allocation ratio of 1:1. The research team responsible for analyzing the data will be kept blind to the participants’ group assignments. The research team will generate the allocation sequence, and the TA will enroll the participants and assign them to the intervention. The trial will adhere to established procedures to maintain separation between staff that take outcome measurements and staff that deliver the intervention [13,14].

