### Setting

This crossover RCT will be conducted on the web and will include health sciences students who are registered in a course on chronic diseases and disability, a third-year undergraduate course at Carleton University in Ottawa, Canada.

Eligible participants will receive comprehensive information about the trial, including the study’s purpose and procedure, through both verbal communication and written materials. To address ethical concerns regarding power dynamics between those responsible for the study and those who may be involved in student teaching and assessment (ie, professors) and students, we opted to involve an individual who is independent of the research team in the recruitment process (ie, a teaching assistant [TA] not involved in other aspects of the study). This decision aims to minimize any potential bias or influence that could arise from direct professor involvement in the recruitment and research. By introducing a TA to be involved in recruitment, we strive to create a more equitable research environment and mitigate any power imbalances that may exist between professors and students. This approach helps ensure that the study is conducted fairly and unbiasedly, fostering a research environment that prioritizes equal opportunities for all participants. Both groups will simultaneously work on an assignment.

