### Participants

#### Inclusion Criteria

The inclusion criteria consist of health sciences undergraduate students who are aged ≥18 years and of any gender identity at Carleton University, Canada. They must be registered in a course on chronic diseases and disability during fall of 2023.

Students who responded to the advertisements and consented to participate in the study will be included. Participant recruitment will involve the TA who is not associated with the research project and does not hold any power or authority over the students. The research assistant (RA) will be responsible for overseeing the consent process. They will ensure that informed consent is obtained from the students voluntarily and without undue influence.

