### Intervention and Measurement

During the initial phase of the study, participants assigned to sequence AB will use ChatGPT (experimental intervention: group A) to complete their assignments, while participants assigned to sequence BA will use conventional web-based tools (control intervention: group B) and serve as a control group. In the subsequent period, the interventions will switch between the 2 groups. Students will not know which one is the “intervention of interest” and which one will be the “comparator.” As mentioned above, the learning activity to be assessed in this project is part of the mandatory course activities. This means that all students will receive a grade for this assignment. Therefore, the instructor will not be able to determine which students have or have not participated in the study. Students’ acceptance to participate in this study only gives permission to the research team to use their data for research purposes, but all students will be assessed for this work as part of the course. The course instructor will not be responsible for grading the assignments associated with the intervention. The TA will be responsible for grading assignments and assigning a unique number code to each participating student, which will be linked to their names. This coded information will be sent to the RA to preserve anonymity throughout the process. The RA will receive the graded assignments, the student names, and their respective codes from the TA. The RA will collect the grades of the student participants and submit them to the research team members responsible for the analysis. It is important to note that the research team, which includes the course instructor, will not have access to the participants’ names. Only the grades and the participant codes will be accessible for analysis. The research team, including the course instructor, will perform the data analysis based solely on the provided grades and participant codes, without access to any identifiable information. This further ensures that anonymity is strictly maintained throughout the analysis phase.

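### The teaching assistant who assigns the tool also grades the assignments with names known, so the stated separation of delivery and outcome measurement does not hold for grades

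*Protocol article*

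**What the plan says.** The article gives the TA these tasks:

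- **Enrolment and assignment** (Randomization and Allocation Concealment): "The research team will generate the allocation sequence, and the TA will enroll the participants and assign them to the intervention".
- **Grading and coding** (Intervention and Measurement): "The TA will be responsible for grading assignments and assigning a unique number code to each participating student, which will be linked to their names".

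It also describes the TA and the safeguards as follows:

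- The trial will follow procedures to "maintain separation between staff that take outcome measurements and staff that deliver the intervention" (Randomization and Allocation Concealment).
- Recruitment is by "a teaching assistant [TA] not involved in other aspects of the study" (Setting).
- The recruiting TA "does not hold any power or authority over the students" (Inclusion Criteria).

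On the analysis side: "The research team responsible for analyzing the data will be kept blind to the participants’ group assignments" (Randomization and Allocation Concealment). Intervention and Measurement adds that the analysis uses grades and participant codes without names. The Abstract labels the trial single-blinded.

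**The concern.** Grading written work is a judgement. A grader who knows which assignment was written with ChatGPT may mark it up or down without meaning to. The usual protection is to keep the person who gives out the intervention away from outcome assessment, or to mask the work before it is graded. The article claims the first, but its own division of labour does the opposite, and it does not mention the second.

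What is at stake is the comparison of grades between tools, which Data Analysis tests with a Wilcoxon test. Two uses of the same grades are also exposed: their Spearman correlation with usability, and the split into low and high performers at a cut-off of 80. There is a second consequence outside the statistics. Setting presents the independent TA as the remedy for power imbalance in recruitment, yet someone who grades mandatory coursework does hold authority over the students.

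**Working it through.** The point rests on the stated roles and on no figure in the plan, so no figure of the plan has to be reproduced.

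**Step 1: roles side by side.**

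| Task | Who, as stated | Section |
|---|---|---|
| Generate the sequence | Research team | Randomization and Allocation Concealment |
| Recruit | TA | Setting; Inclusion Criteria |
| Oversee consent | Research assistant (RA) | Inclusion Criteria |
| Enrol and assign the tool | TA | Randomization and Allocation Concealment |
| Grade the assignments | TA | Intervention and Measurement |
| Issue codes linked to names | TA | Intervention and Measurement |
| Pass grades on for analysis | RA | Intervention and Measurement |
| Analyse | Research team, from grades and codes | Intervention and Measurement |

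The text speaks of the TA in the singular and describes no second one. Assigning the tool, grading, and holding names therefore meet in one role. Nothing says that name or tool is removed from the work before it is graded.

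**Step 2: what a lean does to the grade contrast.** Let τ be the true ChatGPT-minus-conventional difference, π the period-1-minus-period-2 difference (including the change of topic), and λ the grader's average lean toward ChatGPT work. The expected ChatGPT-minus-conventional difference within a student is:

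- sequence AB: τ + λ + π
- sequence BA: τ + λ − π
- mean of the two sequences: τ + λ

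The period term cancels. So does general severity or leniency, because it applies to both of a student's grades. The lean λ does not cancel: it appears only in the sum τ + λ, so no analysis of these data can tell the two apart. One point of lean is one point of bias.

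**Step 3: how large that could look.** The documents give neither the size of any lean nor the SD of within-student grade differences, so both are assumed here. With the article's 45 evaluable students and a paired t approximation (the plan uses Wilcoxon), the 95% half-width is 2.015 × SD / √45. The table also gives the chance of a significant result when there is no true effect.

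| Assumed SD of differences | Half-width (points) | Lean 1 point | Lean 3 points | Lean 5 points |
|---|---|---|---|---|
| 5 | 1.50 | 26% | 98% | >99% |
| 10 | 3.00 | 10% | 50% | 91% |
| 15 | 4.51 | 7% | 26% | 59% |
| 20 | 6.01 | 6% | 17% | 38% |

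The range runs from almost the nominal 5% to near certainty. It shows that the effect depends entirely on unknown inputs and says nothing about this trial in particular.

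**Step 4: the other uses of grades.** A lean moves students across the cut-off of 80. For the Spearman correlation, a uniform shift enters directly if both tools are pooled. Within one tool it leaves the ranks unchanged, and only a lean that differs between students alters the result. That is possible because the grader also knows identities.

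**Step 5: the primary outcome.** SUS is completed by the students in Qualtrics. The TA's grading does not touch it, except through its correlation with grades.

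**The case against.** Three objections carry weight.

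**Grades are not the primary outcome.** Outcomes and Measurements lists learning outcomes as secondary, and Study Hypotheses labels the learning-outcome hypothesis exploratory. This stands and limits the scope. It does not make the point trivial: the null hypothesis and the Abstract's alternative hypothesis both name learning outcomes, and Results and Discussion anticipate similar grades with the two tools. A lean could create a difference or hide one.

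**A reader might infer that the analysts are unblinded**, because the research team both generates the sequence and analyses. The documents do not support that. The blinding sentence covers only those responsible for the analysis, and Intervention and Measurement likewise speaks of members responsible for it, so a subset may be meant. Analysts see grades and codes that the TA issued, and nothing shows that the person who generated the list could match it to the codes. What remains is that the article does not say the two tasks fall to different people. Removing names secures anonymity, which is not the same as blinding to tool.

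**A reader might also infer that nobody in the trial is blind.** That goes too far. Apart from the analysts, the article does not claim that students are blind to the tool. It claims only that they do not know which tool is of interest, and although Setting says they are told the study's purpose, it does not say they are told that. The fair statement is that the article does not make clear whom the single-blind label covers.

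It is also tempting to quote one figure, such as a 3-point lean being significant half the time. At an assumed SD of 10 the half-width is 3.00, so a lean of that size gives about 50% automatically and is no evidence about this trial.

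**Conclusion.** The contradiction is real and can be read directly from the article. The role that assigns the tool also grades the work with names known and no masking stated, against the separation claim in Randomization and Allocation Concealment and the descriptions of the TA in Setting and Inclusion Criteria. The plan therefore states a safeguard that its own roles do not deliver.

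The effect is confined to the secondary learning outcome and the analyses that use grades. Its size is one point of bias per point of lean, and the documents do not allow the lean itself to be estimated. The conclusion assumes that the TA is one person or role throughout, as the text reads, and that no unreported masking took place. Blinding of the analysts is unclear and needs a clarifying sentence; it is not shown to fail.

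**What to change.** 1. Reconcile the TA's role across Setting, Inclusion Criteria, Randomization and Allocation Concealment, and Intervention and Measurement. State who assigned the tool, who graded, and what the grader knew.
2. Results says data collection took place in October and November 2023, so assignment can no longer be reorganised. Where submissions are ungraded or stored, have existing staff who did not assign the tool remove name and tool from the work before grading or regrading. The grading or regrading should be done by someone who did not assign the tool, since the TA may remember it.
3. If that is not possible, withdraw the separation claim and report the grade results as assessed by a grader who knew the tool.
4. In either case, say exactly who is blind under the Abstract's single-blind label.
5. State that whoever generated the list does not analyse, and give the analysts masked tool labels until the analysis syntax is fixed.
6. Sequence generation should not be moved to the RA, who oversees consent, unless the list is generated after consent has closed. Otherwise the repair would weaken allocation concealment.

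The cost is a wording correction and a few hours of existing staff time. The main drawback is that text written with ChatGPT may remain recognizable, so masking would be partial and should be reported as such.

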### Intervention and Measurement

During the initial phase of the study, participants assigned to sequence AB will use ChatGPT (experimental intervention: group A) to complete their assignments, while participants assigned to sequence BA will use conventional web-based tools (control intervention: group B) and serve as a control group. In the subsequent period, the interventions will switch between the 2 groups. Students will not know which one is the “intervention of interest” and which one will be the “comparator.” As mentioned above, the learning activity to be assessed in this project is part of the mandatory course activities. This means that all students will receive a grade for this assignment. Therefore, the instructor will not be able to determine which students have or have not participated in the study. Students’ acceptance to participate in this study only gives permission to the research team to use their data for research purposes, but all students will be assessed for this work as part of the course. The course instructor will not be responsible for grading the assignments associated with the intervention. The TA will be responsible for grading assignments and assigning a unique number code to each participating student, which will be linked to their names. This coded information will be sent to the RA to preserve anonymity throughout the process. The RA will receive the graded assignments, the student names, and their respective codes from the TA. The RA will collect the grades of the student participants and submit them to the research team members responsible for the analysis. It is important to note that the research team, which includes the course instructor, will not have access to the participants’ names. Only the grades and the participant codes will be accessible for analysis. The research team, including the course instructor, will perform the data analysis based solely on the provided grades and participant codes, without access to any identifiable information. This further ensures that anonymity is strictly maintained throughout the analysis phase.

### Experimental Intervention

In this study, the intervention of interest is the use of ChatGPT by students to complete their assignments. As part of this intervention, students will be given a period of 6 days to use it for assignment completion. Along with the assignment instructions, participants will receive an ethical guideline and specific guidelines on how to use ChatGPT effectively (Multimedia Appendices 1 and 2) [18-23].

### Control Intervention

In this study, the control intervention is the use of conventional web-based tools by students to complete the assignment. In this intervention, they will receive instructions on how to complete the assignment using conventional web-based tools available on the internet, without the use of ChatGPT or other generative AI platforms “and” or “or” tools. They will have a timeframe of 6 days to complete the assignment using these conventional web-based tools. Similar to the participants in the experimental intervention, they will also be required to fill out a survey on technology usability, providing feedback on their experience with the web-based tools.

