### Outcomes and Measurements

The outcome measures will be (1) the usability of the technological tools (ChatGPT or conventional) for completing the assignments (primary outcome), (2) the participants’ perception of these tools as support for learning, and (3) the learning outcomes (secondary outcomes). Outcomes and measurements will be collected at 2 points: at the first follow-up, that is, after the first intervention (experimental or control) in the initial phase, and at the second follow-up, that is, after the second intervention (experimental or control) in the final phase (Figure 1).

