#### Usability

Participants in the experimental intervention (AI-ChatGPT intervention) will also be asked to fill out a survey regarding their perception of using generative AI as an assistance tool to complete their assignments. This survey aims to gather insights into their thoughts, opinions, and attitudes toward using AI in their learning experiences. Participants will have the opportunity to share their feedback on the effectiveness, benefits, challenges, and overall satisfaction while using AI for assignment completion. Their responses will provide valuable information on AI technology’s perceived value and acceptance in enhancing their learning experience. Participants in the control intervention (conventional tools) will complete the same survey, but regarding the usability of the conventional tools.

The System Usability Scale (SUS) will assess the participants’ perceptions of usability. The SUS is a valid questionnaire [26] and will be administered at the end of the interventions and when participants cross over to the other assistance tool (AI-ChatGPT or conventional web-based tools without AI). The SUS is commonly used in numerous studies to assess the effectiveness and usability of new technologies, including in the education field [27-29]. A recent systematic review of home-based telerehabilitation software systems for remote supervision revealed that the SUS tool was the most frequently used measure or tool across the studies examined [28]. This scale has been translated into several languages, including the American Sign Language [30-32]. The SUS questionnaire was originally developed as a “quick and dirty” tool, with the goal of providing a fast and nonintrusive assessment experience for participants [26]. The SUS consists of 10 items formulated as affirmative statements, for which users indicate their level of agreement or disagreement on a 5-point Likert scale (1=strongly disagree; 5=strongly agree). For the odd answers (1, 3, and 5), we will subtract 1 from the score that the user answered; for the even answers (2 and 4), the score will be subtracted from 5. The values of the 10 questions will be added and multiplied by 2.5. The final score can range from 0 to 100. Internal consistency will be calculated using Cronbach α per item and overall. This scale allows for the assessment of outcomes and comparisons within and between the 2 interventions (Table 1).

**Table 1 table1:** Overview of outcome measures.

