## Results

Data collection took place in October and November 2023; the anticipated results are scheduled for publication in 2024. We anticipate several key findings. First, randomization is expected to have groups with closely matched demographic characteristics, ensuring a balanced starting point for our analysis. Second, we anticipate that usability will be significantly higher for the ChatGPT intervention than for conventional methods, reflecting the potential benefits of AI-assisted learning. In addition, regarding ChatGPT’s use in assignments, we expect to observe students expressing concerns about data privacy and plagiarism, consistent with prior literature findings on these issues. The potential correlation between usability and learning outcomes is a significant aspect to consider in our study. Understanding how usability impacts learning outcomes not only is critical for this study but also lays the foundation for future investigations. By quantifying the effect sizes of both the learning and usability effects in this study, we can better inform the calculation of sample sizes for larger RCTs on this topic. These data will be invaluable for designing robust experiments and ensuring that our research can provide meaningful insights into the relationship between usability and educational outcomes.

Furthermore, it is our anticipation that despite these concerns, learning outcomes will remain consistent across both interventions. We expect to observe that while these concerns may be raised, the overall effectiveness and educational benefits of ChatGPT are not compromised. Our study seeks to determine whether these anticipated results are confirmed. These data will contribute to a better understanding of the potential impacts of integrating AI into health sciences education.

This study is expected to contribute to the identification of key areas and challenges concerning the use of AI as an educational tool, specifically examining its benefits and challenges for students. By doing so, it aims to facilitate the establishment of comparable frameworks for future academic endeavors. In addition, the findings will enlighten educators about the potential advantages and barriers associated with integrating AI into educational activities for university students.

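### No described measurement records which tools students actually used, so similar grades could reflect generative AI use in the control period rather than equal learning

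*Protocol article*

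**What the plan says.** Under Control Intervention, students are to work "without the use of ChatGPT or other generative AI platforms", and "They will have a timeframe of 6 days to complete the assignment using these conventional web-based tools". Under Setting, "This crossover RCT will be conducted on the web". Under Intervention and Measurement the work is a compulsory part of the course, and "all students will receive a grade for this assignment". No log, transcript, declaration, detection step or proctoring is described.

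Outcomes and Measurements and Table 1 list three things: usability by the System Usability Scale (SUS, primary), perception of the tools, and grades (secondary). On the control-period survey, the Usability section says: "Participants in the control intervention (conventional tools) will complete the same survey, but regarding the usability of the conventional tools". The perception questionnaire follows the ChatGPT period. Its four described sections cover sociodemographics, AI literacy and positive experiences, negative experiences, and accountability, ethics and equity. From the assignments themselves, the analysts receive only grades and participant codes.

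Under Data Analysis, grades are compared by a Wilcoxon test, and no equivalence margin is stated. The Results section expects that "learning outcomes will remain consistent across both interventions" and takes this to mean that ChatGPT's educational value is intact. The Discussion repeats the expectation of similar grades.

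**The concern.** The trial compares two tools, but what separates them is an instruction that students can break in private, in work that counts towards their course result. The article is aware of the problem. Its Background section cites a survey that left open whether students would be candid about using ChatGPT, and it raises academic dishonesty as a concern. Yet nothing in the described measurements captures actual use, and Limitations and Strengths mentions neither adherence nor contamination.

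What is at stake is mainly the grade conclusion. If some control work was done with generative AI, the grade contrast is diluted towards zero whichever tool gives better grades. The authors expect no difference and would read it favourably. With no record of tool use, dilution and true similarity would look the same. Analysts cannot recover this information later if it was never collected.

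**Working it through.** **The plan's own figure.** Sample Size gives 45, raised to 50. A two-proportion formula with 84% against 50%, two-sided 5%, 90% power and continuity correction gives 44 per group, close to 45. The 10% allowance gives 50 (45/0.9 = 50; 45 × 1.1 = 49.5, rounded up). This calculation uses neither grades nor SUS, so it says nothing about the power of the grade comparison. The point here does not depend on it.

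**Inputs for the dilution check.**
- c, the share of control periods in which generative AI was used: not in the documents. Assumed range 10% to 40%.
- δ, the true mean within-student grade difference, and its SD: not in the documents. δ is set to the value that has 90% power when c = 0, so that only the loss from c is shown.
- Two-sided 5% level: z(0.975) = 1.960. 90% power: z(0.90) = 1.282. Sum 3.242.
- A student who breaks the rule is assumed to gain the full AI effect on the grade.

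**Formulas.** Expected difference = δ − cδ = (1−c)δ. With the SD of paired differences unchanged, power = Φ[(1−c) × 3.242 − 1.960]. The number of students needed to restore 90% power is multiplied by 1/(1−c)².

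| c (assumed) | difference kept | (1−c) × 3.242 − 1.960 | power | 45 students would become |
|---|---|---|---|---|
| 0 | 100% | 1.282 | 90% | 45 |
| 10% | 90% | 0.957 | 83% | 56 |
| 20% | 80% | 0.633 | 74% | 71 |
| 30% | 70% | 0.309 | 62% | 92 |
| 40% | 60% | −0.015 | 49% | 125 |

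A paired noncentral t calculation with 45 pairs gives the same percentages. The planned test is Wilcoxon, so these figures are an approximation that shows the pattern.

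**The ChatGPT period.** Use of the assigned tool is equally unrecorded there. If a share m of ChatGPT periods did not use it, the difference becomes (1−c−m)δ. With c = 20% and m = 10%, 70% is kept, the same as the 30% row.

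**The usability score.** The same formula does not carry over. Control students are asked to rate the conventional tools, so a student who used ChatGPT against the rule is still asked about something else. Whether and in which direction the rating moves depends on how that student answers.

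**The case against.** The strongest reply is that this is a condensed article. It describes questionnaire sections, not items. The perception survey includes multiple-choice and short open questions, and the assignment instructions and appendices are not shown. A tool-use item may exist. That stands: a reader might infer that the data cannot show whether the comparison took place, and the documents do not establish this. What they support is that no described measurement does so, although the article sets out its outcomes, survey topics and grade data in some detail.

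Three other inferences also go too far.
- That contamination shrinks the SUS contrast: this does not follow, for the reason given in the working. If it did, it would work against the authors' main expectation of higher usability with ChatGPT.
- That students in sequence AB reach the control period trained in ChatGPT, so that contamination must be unequal: the article says only that "participants will receive an ethical guideline and specific guidelines on how to use ChatGPT effectively". No training session is described. Unequal contamination is plausible but not shown.
- That the work is unsupervised: the article does not say so. It follows only from a 6-day web-based task with no monitoring described.

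It is also fair to say that grades are a secondary outcome, that the exploratory hypothesis predicts a grade difference, and that the power series contains no trial data beyond the 90% starting point. The missing equivalence margin would weaken a claim of similarity even without contamination. Finally, comparing students as randomized remains a valid comparison of two instructions. None of this removes the point: the authors draw conclusions about the tools, not about the instructions.

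**Conclusion.** The point holds for the grade comparison, conditionally. The contrast rests on an instruction, and no described measurement shows whether it was followed in either period. If generative AI was used in a share c of control periods with full effect, the expected grade difference falls to (1−c) of its true size. Power falls from 90% to about 83%, 74%, 62% or 49% at c of 10%, 20%, 30% or 40%. These rates are assumptions, and so are the full effect in non-adherent students and the unchanged SD. The actual rate could be near zero, but nothing described would show that.

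A non-significant Wilcoxon test on grades would therefore not support the reading in the Results section that educational value is preserved. No direction of bias can be claimed for the primary usability outcome. The gap should be closed or disclosed, but it does not invalidate the as-randomized comparison.

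**What to change.** - In both periods, add one identical item to the Qualtrics survey: which tools were used for this assignment, including any generative AI, and for roughly what share of the work. Tell students that the answer does not affect the grade. Keep it from the teaching assistant, who both grades the work and holds the link between names and codes.
- Report the rate of non-adherence by period and sequence beside the grade result.
- Keep the as-randomized comparison primary. Any analysis by reported tool use should be supportive only, because it conditions on behaviour after randomization and can bring in bias of its own.
- The Results section says data were collected in October and November 2023. If no such item was collected and it can no longer be obtained, name possible contamination under Limitations and Strengths, and do not present a non-significant grade difference as evidence of similar learning outcomes.

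The cost is one short item per period and a few lines of reporting or, after collection, a change of wording only. The drawback is that self-report may under-count prohibited use, so a low reported rate would reassure only in part.
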